### Contextual factors measured at the individual and community level

Data describing contextual factors that characterize the nutrition, physical and tobacco environments of communities from which participants are recruited as well as individual behaviors in these domains are collected using the modified EPOCH-1 and modified EPOCH-2 questionnaires modified from the PURE study [57, 58]. EPOCH-1 is a standardized community audit developed and validated in the PURE study [57] and EPOCH-2 captures individual’s perceptions of their food, activity, and tobacco environment also developed in the PURE study [58] with added questions on social ties, alcohol use, and workplace activity and food choices and behaviors.

### Community audits

To study community level contextual factors as related to individual risk factors and clinical events we retrospectively defined “community” as participants are already recruited. After review of the communities from which participants in the 5 CPTP cohorts and the 2 partner cohorts originate, the forward sortation areas (FSA) was deemed to be the optimal community unit. (Table 5) We have chosen the FSA as our definition of community because: 1) there was low representation of cohort participants from census tracts in rural areas and eastern provinces of Canada, 2) the FSA are those reported by census respondents for their place of residence and this information collected from the census is available in aggregate for each FSA. This census information includes age, sex, marital status, families and household information, housing costs, mobility and migration, immigration and citizenship, income and earnings, and ethnic groups. This is balanced by some limitations of this approach include: for certain highly populated urban areas the FSA is too large to well represent the community—in this scenario, we surveyed multiple postal codes within the FSA to capture the diversity. The community level information will be used together with self-reported perception of community environment as well as behavior patterns, ie shopping, activity, and workplace. These will be used together with objective measures of the built environment from publically available databases (ie streetsmart walk-score at www.walkscore.com), which provides information by postal code on neighborhood walkability, land use mix, transportation availability and location of food retail outlets [59].

**Table 5 Tab5:** Number of FSAs represented by the 7 Cohorts making up the CAHHM

Province	FSA total	FSA to be assessed in CAHHM (Postal Codes)*	# in reliability assessment (%)	Number of postal codes within FSAs being assessed (sum)
BC	190	190 (+50)		112904
AB	153	153 (+46)	40 (21.1 %)	76924
SK	49	49 (+8)		21541
MN	66	66 (+12)		23943
ON	526	526 (+208)		282123
QC	419	419 (+108)	55 (10.4 %)	215565
Atlantic	230	230 (+72)		92809
NS	77	77 (+26)		28171
NB	111	111 (+30)		59530
PEI	7	7 (+2)		3995
N/L	35	35 (+14)		1113

*For FSA with income discrepancies across postal codes within the FSA, 2 audits were done to reflect the 25^th^ percentile an

### Social capital and social ties

A series of validated questions were used to measure social support from the family and the wider social environment and included questions such as participation in community organizations, civic engagement, perceived social standing, and intensity of social relationships with close confidants, and type of contact with confidants (ie in-person, telephone, email, Facebook, text messages).

### Culture and immigration

Among immigrants to Canada we will probe the reasons for immigration (economic, family, refugee) and the socio-cultural connections they have made since immigration using the Immigration Questionnaire [60] and the Vancouver Inventory of Acculturation [61]. This information will be used along with measures of socioeconomic status (education, household income, employment and marriage) which has already been collected in each of the participating cohorts.

### Access to and quality of health care services

A health services questionnaire was developed to collect information at the individual level and will be supplemented by record linkage to administrative, laboratory and clinical databases available in various Canadian provinces. With these data sources we plan to analyze existing population-based databases to create unique community-level profiles of access and quality of health care services including the rates of selected CV related diagnostic tests and treatments. This will be a unique component of this initiative because health care services have not been a focus of most traditional cohort studies to date and yet, it is increasingly recognized that quality of health care provided to individuals can play a major role in determining their likelihood of suffering and surviving clinical events [62]. Furthermore, how Canadians with CV risk factors are managed likely varies across the country due to factors such as physician and allied health care personnel availability, type and nature of primary care services, patient education, and socioeconomic status.

### Inclusion criteria

Participants between ages 35 and 69 y (inclusively) at time of screeningProvision of Informed ConsentThe participant is willing to undergo an MRI scan

### Exclusion criteria

Participant is claustrophobic and/or is known to suffer from moderate to severe anxiety during MRI scans or similar proceduresParticipant is obese and/or exceeds equipment weight limit and/or circumference of the MRI portal at time of screeningParticipant has a metallic implant or another foreign body which is not compatible with Magnetic Resonance Imaging (MRI) (eg pacemakers, defibrillator, vascular clips, drug pumps, implant(s), or any other foreign bodies, extensive tattoo covering a large part of their chest or head)Female participants that are or may be pregnant (confirmed or uncertain)Received an MRI contrast agent within 72 h prior to the MRI scan.

#### Record linkage with health administrative databases

Data collected of participants from the CAHHM will be linked with health care administrative databases, available in various provinces, for ascertainment of cardiovascular-related health care services before and after enrollment in the study as well as long-term CVD outcomes. (Table 6) The International Classification of Diseases (ICD) codes that will be used to measure various outcomes have been validated and described in detail elsewhere [63]. Most provincial health care administrative databases in Canada contain a patient health card number as a unique identifier that enables efficient deterministic data linkage of various data sets, in this instance cohort data sets with province- or region-specific administrative databases. To protect patient privacy, the health card number (HCN) in each database is typically scrambled creating another unique anonymized identifier before the actual data linkage. All participants were asked on the informed consent if they were willing to provide HCN as part of their parent cohort participation or as a new request (and thus far out of the first 1000 participants 99.2 % have consented to provide their HCN). Due to the federated nature of the health care system in Canada, there is no single repository of administrative databases. As a result, data linkage activities will involve working with multiple data custodians and governments across the country, and will require understanding of and compliance with each province’s health information privacy legislation. The Alliance is planning to work with key data custodians such as the Canadian Institute for Health Information (CIHI), which collects hospital discharge abstracts for the entire country except for Quebec, Statistics Canada which houses the Canadian Mortality Database and the Canadian Cancer Registry and various provincial health services research units located across Canada including the Institute for Clinical Evaluative Sciences (ICES) in Ontario, Population Data BC, the Population Health Research Unit, Dalhousie University, Régi de l’assurance maladie Québec (RAMQ), etc. - each of which hold administrative databases for their region/province.

**Table 6 Tab6:** Health system quality indicators

Health system quality indicators measurable from the CPTP CVD Survey
Participants with a family doctor
Difficulties accessing primary or specialist care
Weight assessment by a health professional
Screening for hypertension, diabetes, hyperlipidemia
Diabetics who have had eyes examined by an ophthalmologist, feet examined, urine protein tested
Smokers who have been offered smoking cessation counseling and/or stop smoking aids
Hypertensives who have their blood pressure treated and controlled
Participants with hyperlipidemia who have been treated with medication to control their blood cholesterol levels
Participants with atrial fibrillation who have been treated with blood thinners
Health system indicators measurable from administrative data
A. Structural variables
# of family doctors/specialists per capita
#, costs and types of ambulatory care visits
#, costs and types of hospitalizations
B. Processes of Care
CV and non-CV medications (statins, ACE inhibitors, diuretics, Beta-blockers)
Laboratory screening rates (lipids, diabetes)
Lab results (lipids, diabetes)
ECG, Stress Test, Echo, CT scans, MRI scans
Cardiac Catheterization
PCI
Cardiac Surgery
C. Outcomes
Myocardial Infarction (STEMI/NSTEMI, unstable angina)
Congestive Heart Failure
Stroke (Ischemic/Hemorrhagic/TIA)
Death (including cause of death)
Atrial Fibrillation
Diabetes and Hypertension

### Study outcomes

#### Primary outcomes

The primary outcomes include MI, Stroke, angioplasty, percutaneous coronary interventions, coronary artery bypass graft surgery, and other important chronic disease outcomes and death. Associations between contextual factors, CV risk factors and MRI markers will be evaluated with these outcomes individually and as a composite measure of CV events.

#### Secondary outcomes

Secondary outcomes for this project include:Congestive Heart Failure requiring hospitalization

#### New onset established risk factors using validated alogrithms [63, 64]

Incident diagnosis of diabetes by physicianIncident diagnosis of hypertension by physicianIncident diagnosis of significant cognitive dysfunction (ie dementia) by physician.

#### Risk markers acquired through imaging and blood samples

Acquired parameters that are linked to the present health statusCandidate parameters for predicting cardiovascular events which affect cardiac and cognitive dysfunction. For further details, please refer to the outcomes in the questionnaires and the MRI protocol described in the Design and Methods section above.

## Statistical considerations

### Power

#### Risk factor proportions

The proportion of risk factors will be examined across cohorts and overall. It is anticipated given the roughly representative subcohorts that recruitment of the target sample of 7000 will provide high power to compare the relative frequency of risk factors comparing men and women, participants across age strata and between non-First Nations and First Nations' Participants.

#### Risk factors to MRI findings

The prevalence of traditional CV risk factors will enable determination of the relative risk of the risk factors on subclinical MRI findings of RWMA, covert stroke and liver adipose tissue. For example, if among 7000 CAHHM participants the frequency of hypertension is 25 % and the frequency of covert stroke is 6.6 %, we will have a high power to detect a relative risk of hypertension on silent stroke of brain of 1.5 (95 % CI: 1.36 to 1.65).

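### The interval labelled 95 % for the hypertension–covert stroke relative risk (1.36 to 1.65) does not follow from its own inputs, which give about 1.25 to 1.81

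*Protocol article*

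**What the plan says.** The section Risk factors to MRI findings (Protocol article, Statistical considerations, Power) illustrates what the cohort can show about risk factors and subclinical MRI findings. The example is conditional: "if among 7000 CAHHM participants" "the frequency of hypertension is 25" % and "the frequency of covert stroke is 6.6" %, then "we will have a high power to detect a relative risk", namely "relative risk of hypertension on silent stroke of brain of 1.5". The interval in parentheses, labelled 95 %, is "CI: 1.36 to 1.65".

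No reference is attached to the interval, no further inputs are given, and no calculation is shown. It therefore reads as the precision expected from the four inputs in the same sentence. The section gives no number for the power; the next one, MRI to clinical events, glosses high power as more than 90 %.

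**The concern.** The example implies 462 covert strokes in all (7000 × 0.066), about a third of them in the exposed quarter of the cohort. With so few cases, limits within about 10 % of the point estimate on either side look too tight for 95 % confidence.

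This is the only numerical statement of precision for the aim of relating risk factors to MRI findings; Table 7 concerns MRI markers and later clinical events. Taken at face value, an observed relative risk of 1.5 would come with a lower limit of 1.36. If the label is wrong, the reader is given a more precise estimate than 7000 participants can deliver.

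**Working it through.** **Inputs**, all from the section Risk factors to MRI findings: N = 7000; hypertension 25 %, so 1750 exposed and 5250 unexposed; covert stroke 6.6 %, read as the overall frequency; relative risk (RR) 1.5.

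**Step 1: risks and cases.**
- Unexposed risk: p0 = 0.066 / (0.75 + 0.25 × 1.5) = 0.066 / 1.125 = 0.0587.
- Exposed risk: p1 = 1.5 × p0 = 0.0880.
- Cases: 1750 × p1 = 154 and 5250 × p0 = 308, total 462.

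**Step 2: standard error.** SE(ln RR) = √(1/154 − 1/1750 + 1/308 − 1/5250) = 0.0948.

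**Step 3: attempt to reproduce the printed figure.**
- With the 95 % multiplier: 1.5 × exp(±1.96 × 0.0948) = 1.246 to 1.806. This is not the printed interval.
- With a multiplier of 1: 1.5 × exp(±0.0948) = 1.364 to 1.649, which rounds to the printed limits at both ends.

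**Step 4: size of the gap.**
- Printed half-width on the log scale: ln(1.65 / 1.36) / 2 = 0.0966, which is 0.0966 / 0.0948 = 1.02 standard errors, or about 69 % coverage (67.5 to 71 % allowing for rounding of the limits).
- Correct half-width: 1.96 × 0.0948 = 0.186. Ratio: 0.186 / 0.0966 = 1.92 (1.86 to 1.99 with rounding).
- For the printed limits to be a 95 % interval, the standard error would have to be 0.1933 / 3.92 = 0.0493. That needs N = 7000 × (0.0948 / 0.0493)², about 25,800, or a covert stroke frequency of about 20 %.

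**Step 5: other readings of the inputs.** 95 % limits at N = 7000:

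| Reading | Limits |
|---|---|
| 6.6 % is the risk in the unexposed | 1.26 to 1.79 |
| 6.6 % is the risk in the exposed | 1.21 to 1.86 |
| Poisson standard error | 1.24 to 1.82 |
| Schoenfeld-type standard error | 1.22 to 1.85 |
| 1.5 is an odds ratio | 1.23 to 1.84 |
| Linear-scale (delta) interval | 1.22 to 1.78 |
| Covert stroke 6.9 %, as in Table 7 | 1.25 to 1.80 |

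None comes near 1.36 to 1.65. Under the main reading, a 90 % interval (1.28 to 1.75) and an 80 % interval (1.33 to 1.69) are also too wide. Raising N to 10,000 gives a 95 % interval of 1.28 to 1.75, still too wide.

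**Step 6: simulation.** In 200,000 binomial draws from 1750 at 0.0880 and 5250 at 0.0587, the 2.5 and 97.5 percentiles of the estimated relative risk were 1.24 and 1.80. The 15.9 and 84.1 percentiles, which correspond to plus or minus one standard deviation, were 1.36 and 1.65.

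**Step 7: power.** A two-proportion test at two-sided 5 % gives 98 %. The log-scale approximation is ln(1.5) / 0.0948 = 4.28; 4.28 − 1.96 = 2.32; power about 99 %.

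**The case against.** The best defence is that little depends on this number. It is a parenthesis in an illustrative sentence whose claim is high power, and that claim holds. The corrected interval still excludes 1. The target of 7000 is not derived from it, and Table 7 deals with another aim and does not use it. All of this stands and limits the severity. It does not make the printed limits a 95 % interval.

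The replacement is also conditional. It is a crude two-by-two interval that assumes all 7000 participants have a usable brain MRI, whereas the Analysis section plans multivariable models and Table 7 considers samples down to 5000. At 5000 the same calculation gives 1.20 to 1.87. The new figure should be labelled accordingly.

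Three stronger readings are tempting but unsupported:

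- A reader might infer that the 1.96 multiplier was certainly omitted. The match to two decimals is strong evidence, but the article shows no calculation, and an interval taken from an outside study cannot be fully excluded, although none is cited. What can be said is that the limits do not follow from the inputs and are consistent with plus or minus one standard error.
- A reader might infer that the study is underpowered for this aim or that other figures share the error. Power is 98 to 99 % under the stated inputs, and the power sections print no other planning confidence interval.
- A reader might see a contradiction between a relative risk here and the logistic models in the Analysis section. Planning on one scale and modelling on another is common, the article does not fix which measure will be reported, and relative risks can be derived from a logistic fit. For this example the scales barely differ: (0.0880 / 0.9120) / (0.0587 / 0.9413) gives an odds ratio of about 1.55 against a relative risk of 1.5.

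**Conclusion.** The point holds as a minor but definite numerical error. An interval labelled 95 % has about 69 % coverage under the inputs printed beside it, and the stated precision is about 1.9 times too narrow on the log scale. The lower limit is about 1.25 rather than 1.36, and the upper about 1.81 rather than 1.65.

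This rests on an unadjusted comparison of two proportions, all 7000 participants contributing, and 6.6 % being the overall frequency of covert stroke. Taking it as the unexposed or exposed risk moves the limits to 1.26 to 1.79 or 1.21 to 1.86, which leaves the conclusion unchanged. The cause of the discrepancy is inferred, not shown.

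**What to change.** In Risk factors to MRI findings, replace the interval with a 95 % interval of about 1.25 to 1.81, stated to be unadjusted and under the inputs given. Alternatively, keep the printed limits and relabel them as plus or minus one standard error. If the limits came from an outside study, cite it and say that they are not the precision expected from 7000 participants.

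The cost is one less favourable figure or one changed label. The power statement can stay, and sample size, data collection and planned models are unaffected.

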#### Analysis

To investigate the association between risk factors and subclinical MRI findings linear (visceral fat) and logistic (RWMA, covert stroke, liver fat %) regression models must be built separately for each MRI outcome used as the dependent variable. Exposures such as age, sex, ethnicity, history of hypertension, diabetes, waist circumference, apolipoprotein B/A ratio, current smoking, physical activity, selected dietary (ie prudent diet score, or ratio polyunsaturated fat/saturated fat), and measures of cognitive function (ie when covert stroke is the outcome) will first be tested univariately, and exposures with a *P* < 0.10 will be taken forward and tested in multivariate regression models. If ethnicity is found to be an independent predictor of an MRI outcome, it will be tested with a composite CV risk score for an interaction with the outcome.

After 5 years, when enough CVD events have been accrued and ascertained through record linkage, the MRI subclinical exposure of covert stroke, global or regional ventricular function abnormalities, liver fat and visceral fat will be tested versus CVD and death to determine their predictive value of clinical events using the area under the curve (C statistics), and net reclassification improvement methods [68].

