### MRI Protocol

Details of the CAHHM MRI protocol are found in Tables 3 and 4. The protocol was developed in collaboration with a multi-disciplinary expert group (see working groups listed at the end of the conclusion section) balancing the scientific objectives with time efficiency. The protocol uses validated standard techniques and provides information on morphology, function and tissue characteristics. Quantitative data are measured or calculated wherever possible. Aside from established parameters, novel markers are included, with most of them being acquired by additional images as part of an extended protocol, performed with the MR contrast agent gadobutrol.

**Table 3 Tab3:** MRI key measures in Heart, Brain, Abdomen during Standard MRI Protocol

Standard		
Sequence	Approximate Imaging Time (min)	Outcome Measure
Cardiac		
2D Cine SSFP (short axis only)	10	LV global (EF) and regional wall motion abnormalities function
		LV mass index
		LV end-systolic volume index
		LV mass-to-volume ratio
		LA size and function
		RV volume and global function
Brain		
3D T1w MPRAGE	8	Brain Volume
2D Flair	3	Covert stroke and white matter lesion burden
Abdomen		
T1w TSE abdominal adipose tissue sequence	2	Visceral fat area
Liver 2D multi-echo gradient-echo sequence	1	Liver fat %
Cerebrovascular		
3D T1w MPRAGE	6	Plaque volume and intraplaque hemorrhage detection
TOF	6	Plaque volume and intraplaque hemorrhage detection
Additional time for positioning		
Coil Positioning	6	
Total time	42^a^	

^a^Note this varies depending on: Scanner make and model, hardware and software used for scanning, need for switching MR coils, participants heart rate, and MRI technologist experience

**Table 4 Tab4:** Extended MRI Scan Protocol

Extended		
Sequence	Approximate Imaging Time (min)	Outcome Measure
Cardiac		
Cine SSFP (3 long axis views and 10–15 short axis views)	12	LV global (EF) and regional wall motion abnormalities function
		LV mass index
		LV end-systolic volume index
		LV mass-to-volume ratio
		LA size and function
		Circumferential strain
		RV volume and global function
Phase-contrast cine	4	Aortic elasticity
LGE	12	Myocardial fibrosis
T1 Mapping	10	Diffuse fibrosis
T2 star-weighted sensitive sequence	10	Microvascular function
Brain		
3D T1w MPRAGE	8	Brain Volume
PD/T2	4	Covert stroke and white matter lesion burden
T2 star-weighted gradient echo sequence	4	Presence of microbleeds
2D resting state fMRI	4	Functional connectivity

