### Covert stroke and cognitive dysfunction

Recent population-based studies have shown that the prevalence of unrecognized “covert” brain infarcts is as high as 30–40 % in the elderly/geriatric population, and current evidence is sufficient to document that covert strokes and ischemic white matter damage in the elderly are associated with cognitive impairments despite the lack of association with specific symptoms, and are highly predictive of future stroke and dementia. However, important gaps in knowledge include the prevalence of brain infarcts prior to age 60 (as previous studies have focused on the elderly), the predictive power of covert stroke and ischemic white matter damage as a marker of important CV events in addition to future stroke (such as myocardial infarction), and the relationship between covert stroke and subclinical manifestations of CVD in other organs. Additionally, both covert stroke and ischemic white matter damage are partly heritable but the genetic basis of this risk has not been well defined yet.

Emerging evidence suggests that alterations in brain structure and function accrue years before clinical symptoms of stroke or cognitive dysfunction. In Alzheimer’s disease, regional brain atrophy and altered glucose metabolism can be detected on neuroimaging 15 years before the onset of symptoms [39]. By contrast, the changes in brain structure and function associated with CV and cerebrovascular disease are largely unknown, because previous population-based studies used last-generation MRI technology without high resolution imaging. We expect that changes in brain structure (eg as measured by volumetric brain MRI) and brain functional and structural connectivity (eg as measured by resting state functional MRI and diffusion tensor imaging of white matter tracts) can be detected in association with CVD such as hypertension and diabetes, both in the presence and absence of MRI-visible signs of irreversible ischemic damage (that is, covert stroke and ischemic white matter damage). This hypothesis will be addressed in the Alliance for Healthy Hearts and Minds, in which high-resolution brain MRI imaging and a comprehensive assessment of CV risk are collected.

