### Incidental findings (CIF)

Four core labs separately assess the Brain (Calgary or Sunnybrook), Cardiac (Montreal Heart Institute), Carotid (Sunnybrook) and Abdomen (IUCPQ). The readers follow a standardized reading protocol. Results are sent to the central project office, where they are linked with the clinical data. These severe structural abnormalities are reported back to participants and their primary care physicians if they consented to this on their informed consent. (Fig. 1) The severe structural abnormalities are shown in the Table 8. The letter emphasizes that this is a research scan which should be followed up with a targeted clinical scan organized by the primary care physician.

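### The covert stroke model lists cognition, which the article treats as a likely consequence of covert stroke, as an exposure; this can bias estimates for factors that affect cognition by another path

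*Protocol article*

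**What the plan says.** The Analysis section of the protocol article gives the purpose of these models as "To investigate the association between risk factors and subclinical MRI findings", with a separate model for each MRI outcome and a logistic model for covert stroke. The candidates begin "Exposures such as age, sex, ethnicity, history of hypertension, diabetes, waist circumference" and continue through lipids, smoking, activity and diet. The list ends with "measures of cognitive function (ie when covert stroke is the outcome) will first be tested univariately". Candidates with P < 0.10 "will be taken forward and tested in multivariate regression models". The cognitive measures collected at baseline are DSS and MoCA (Table 2). If ethnicity proves to be an independent predictor of an MRI outcome, an interaction test with a composite risk score follows.

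Other sections place cognition after covert stroke, or among the things the study factors act on:

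- Covert stroke and cognitive dysfunction: "covert strokes and ischemic white matter damage in the elderly are associated with cognitive impairments", and these lesions are said to foretell later stroke and dementia.
- Cognitive function: the DSS score is described as lower in people with a silent brain infarct, and as showing age effects.
- Abstract, Discussion: cognitive function is named beside subclinical vascular disease as something on which community factors, behaviours and access to care have an impact.
- Data management and data access: the assessments not completed online, which include cognitive testing, are done at the MRI site just before or after the scan.

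**The concern.** The covert stroke model is meant to show which risk factors are related to covert stroke. The section Risk factors to MRI findings describes its target as the relative risk of those factors on the MRI finding. A cognitive score taken at the scan visit is not an earlier exposure in the article's own account; it is closer to a result of the infarct already visible on the scan.

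Once such a variable is in the model, the coefficient for hypertension compares people with the same cognitive score. If hypertension also lowers cognition without a visible infarct, a hypertensive person's low score is partly explained by the hypertension. The score then points less to a covert stroke, and the model assigns a smaller effect to hypertension. At stake are the reported effects of the factors the study wants to rank, and any decision that depends on a coefficient from this model.

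**Working it through.** **Inputs from the article.** N = 7000, hypertension 25 %, covert stroke 6.6 %, relative risk 1.5 (Risk factors to MRI findings). Screening level P < 0.10 (Analysis).

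**Assumed inputs.** The article gives no value for dY, the number of SDs by which covert stroke lowers the cognitive score, or dX, the number by which the risk factor lowers it directly. Ranges are shown below.

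**1. The plan's own figure.**
- Risk without hypertension: 0.066 / (0.75 + 0.25 × 1.5) = 0.0587. With hypertension: 1.5 × 0.0587 = 0.0880.
- Expected covert strokes: 0.0880 × 1750 = 154 and 0.0587 × 5250 = 308.
- Power at two-sided 0.05 (alpha assumed) is 0.98, which agrees with the article's claim of high power.
- SE of the log relative risk: √(1/154 − 1/1750 + 1/308 − 1/5250) = 0.095, so the 95 % interval is 1.25 to 1.81. The stated 1.36 to 1.65 matches plus or minus one SE. That is a separate matter, and nothing below rests on it.
- Odds ratio: (0.0880/0.9120) / (0.0587/0.9413) = 1.548, log OR 0.437.
- SE of the log OR: √(1/154 + 1/1596 + 1/308 + 1/4942) = 0.103.

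**2. Would cognition pass the screen?** With 462 covert strokes (7000 × 0.066) against 6538 without, the power to reach P < 0.10 is 0.67, 0.99 and above 0.999 for a true difference of 0.1, 0.2 and 0.3 SD. The screen is therefore unlikely to keep cognition out.

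**3. Effect of conditioning on cognition.** Let C = e − dY·Y − dX·X, with e standard normal, Y covert stroke and X the risk factor. By Bayes' rule,

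logit P(Y=1 | X, C) = logit P(Y=1 | X) + log[f(C | Y=1, X) / f(C | Y=0, X)].

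The last term equals −dY²/2 − dY·C − dY·dX·X. The coefficient of X is therefore

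adjusted log OR = true log OR − dY·dX.

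Starting from OR 1.548:

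| dY | dX | shift in log OR | adjusted OR | share of log OR lost |
|---|---|---|---|---|
| any | 0 | 0 | 1.55 | 0 % |
| 0.3 | 0.1 | −0.03 | 1.50 | 7 % |
| 0.2 | 0.2 | −0.04 | 1.49 | 9 % |
| 0.3 | 0.3 | −0.09 | 1.42 | 21 % |
| 0.5 | 0.2 | −0.10 | 1.40 | 23 % |
| 0.5 | 0.5 | −0.25 | 1.21 | 57 % |

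The same −0.10 shift takes an OR of 1.57 to exp(0.451 − 0.10) = 1.42. Logistic regression on 1,000,000 simulated participants agreed: at dY 0.5 and dX 0.2 the OR fell from 1.540 to 1.393, a change of −0.10 in the log.

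**4. Which factors does the article link to cognition by another path?** Age, because DSS is said to vary with age. Hypertension and diabetes, because the authors expect brain changes with them whether or not ischaemic damage is visible. That expectation concerns brain structure and connectivity, so a lower test score is one step further. The article shows no such path for smoking, diet, apolipoproteins or ethnicity.

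**The case against.** The article says association, both for the aim of the model and for the link between covert stroke and cognition. The causal order is inferred, and long-standing low cognition could precede vascular disease. Cognition is only screened and tested, and the article does not say it stays in a final model. The bias also vanishes for a factor that reaches cognition only through covert stroke. At the small end, a shift of 0.03 is about a third of the SE of 0.103. All of this stands as a limit on the size and reach of the point. It does not remove it: the article names cognition as an exposure for this one outcome, and its other sections support only the reverse order.

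Two stronger readings are tempting. A reader might infer that every risk factor effect, including ethnicity, is biased. The algebra does not allow that where dX = 0, and the article shows no separate path for ethnicity; it even calls DSS independent of language.

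A reader might also infer that the ethnicity estimates are distorted by how covert stroke is detected. Table 3 reads it from one sequence ("2D Flair 3 Covert stroke and white matter lesion burden"), Table 4 from another ("PD/T2 4 Covert stroke and white matter lesion burden"), two brain laboratories are named, and no such term appears in the model. The documents do not support this. The exposure list is open, and technical covariates may sit in an analysis plan that is not shown. The readers follow a standardized protocol. Neither unequal sensitivity nor an uneven spread of scan types over ethnic groups is stated.

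**Conclusion.** The point holds for cognition as an exposure in the covert stroke model. It can bias the estimates for age, hypertension and diabetes, and for any other factor that relates to cognition apart from covert stroke. The direction is towards the null when the factor raises covert stroke risk and lowers cognition. The shift is dY × dX on the log odds scale, under a normal cognitive score with additive effects. Both quantities are assumptions, so the documents fix the mechanism but not the size: over the range shown, the loss runs from nothing to about half of the log OR. At 0.5 and 0.2 SD it is roughly one standard error of the hypertension estimate. The change is worth making before analysis, but the documents do not show that it would overturn a conclusion.

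**What to change.** - Remove DSS and MoCA from the candidate exposures of the covert stroke risk-factor model.
- Analyse cognition as an outcome in its own model, with covert stroke and white matter burden as exposures.
- If a covert stroke model with cognition is kept, for example to see how well test scores indicate a lesion, label it descriptive. Do not take risk-factor or ethnicity effects from it, and do not let it trigger the ethnicity interaction test.

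The cost is a change of wording in the analysis section and one additional model. No new data are needed, since DSS, MoCA, covert stroke and white matter burden are already among the study measures.
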